### **7.3.6. Serious adverse events (SAEs)**

SAE is any experience that suggests a signification hazard, contraindication, side effect or precaution. With respect to human clinical experience this includes any event which:

- ◆ results in death,
- ◆ is life-threatening,
- ◆ requires inpatient hospitalization or prolongation of hospitalization, unless hospitalization is for:
  - routine treatment or monitoring of the studied indication, not associated with any deterioration in condition.
  - elective or pre-planned treatment for a pre-existing condition that is unrelated to the indication under study and has not worsened since the start of study drug
  - treatment on an emergency outpatient basis for an event not fulfilling any of the definitions of a SAE given above and not resulting in hospital admission
  - social reasons and respite care in the absence of any deterioration in the patient's/subject's general condition
- ◆ results in persistent of significant disability / incapacity, or
- ◆ is a congenital anomaly/birth defect,
- ◆ is a significant or important medical event that, based on appropriate medical judgment, may jeopardize the patient/subject or may require intervention to prevent one of the other outcomes listed above.

### **7.4. Sera cryopreservation**

For subjects who agree on ancillary study, the residue samples of immunogenicity test will be preserved in a -80°C freezer for further research.

## **8. Safety Monitoring**

### **8.1. Serious adverse events reporting requirement and emergency procedures**

Whether or not related to the study medication, any adverse event which is fatal or life threatening occurred during the study must be reported promptly (within 24 hours) to Contract Research Organization (CRO), Qualitix, [contact]; Fax: (02)

[name], and Qualitix will inform NHRI on the same day. At the time of the reporting, the following information should be provided if possible: study center, subject number, study phase during which the event occurred, a description of the event, date of onset and current status, outcome, action taken with the investigational vaccine; the reason why the event is classified as serious; and the investigator's current assessment of the association between the event and investigational vaccine.

Within the required timeframe, the investigator must provide further information on each serious adverse event to Qualitix, and Qualitix will assist investigator to submit to each IRB, ADR reporting center, NHRI and DSMB.

Each recurrent episode, complication, or progression of the initial SAE should be reported as a follow-up to the original episode within 24 hours of the investigator's receiving the follow-up information. An SAE occurring at a different time interval or otherwise considered completely unrelated to a previous one should be reported separately as a new event.

## **8.2. Pregnancies**

All female subjects will be instructed to use adequate contraceptive precautions until 2 months after completion of the vaccination series ([Section 7.3.2](#)). To ensure participant's safety, each pregnancy in a subject who has received study vaccine must be reported to Qualitix within 24 hours of learning of its occurrence (either from the result of urine pregnancy test or the verbal information). Qualitix should inform NHRI on the same day. The pregnancy outcomes, including spontaneous or voluntary termination, details of the birth, and the presence or absence of any birth defects, congenital abnormalities, or maternal and/or newborn complications, will be followed. Any SAE experienced during pregnancy should be reported as well.

## **8.3. Data Safety Monitoring Board (DSMB)**

The Data and Safety Monitoring Board (DSMB) will act in an advisory capacity to monitor participant safety and evaluate the suitability of second part of study.

### **8.3.1. DSMB responsibilities**

The DSMB responsibilities are to:

- ◆ review the study protocol, informed consent documents and plans for data safety and monitoring (refer [Section 8.3.2](#));
- ◆ protect the safety of the study participants;
- ◆ consider factors external to the study when relevant information becomes available, such as scientific or therapeutic developments that may have an impact on the safety of the participants or the ethics of the trial;
- ◆ review interim analyses in accordance with stopping rules, which are clearly defined in [Section 8.3.3](#) and have the approval of the DSMB;
- ◆ make recommendations to the NHRI, the Principal Investigator (PI), and, if required, to the Taiwan Food and Drug Administration (TFDA) concerning continuation, termination

or other modifications of the trial based on the observed adverse events/serious adverse events of the vaccination under study;

- ◆ make recommendations and assist in the resolution of problems reported by the PI;
- ◆ assist the NHRI by commenting on any problems with study conduct and/or data collection.

The DSMB will discharge itself from its duties when the study is complete.

### **8.3.2. DSMB process**

The study could be initiated only after an independent DSMB has reviewed the relevant study materials. 14 days after the last subject of Part 1 has received the second vaccination dose, DSMB will review the initial safety data for each of these 10 study subjects. If no SAE happens prior to interim analysis, the DSMB will recommend continuation of the study recruitment for Part 2.

Throughout the study period in either Part 1 or Part 2, if any vaccine related SAE or serious complaints happen, the PI has to inform DSMB about the event. The DSMB is to make a decision on whether the SAE meets the stopping criteria of the study (see [Section 8.4](#)) and conclude if further enrollment of the subjects in the study should be continued or suspended, and will inform the NHRI and PI accordingly. The PI is to inform the NHRI about the study status at the same time. The sponsor is responsible to make the final decision about further enrollment and continuation of the study.

An emergency DSMB meeting can happen any time during the study period.

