### 8.3.5. Reports from the DSMB

The results from the DSMB will be distributed in a pre specified way without any possibilities for changes. The formal DSMB report should indicate that:

- ◆ the study should continue without any changes, or
- ◆ the study should be stopped\* if any of the criteria occur that are defined as study stopping rules in the protocol.

\* This recommendation should be made by formal majority vote. If this should be the case, a specified report will be created and distributed to the NHRI.

Once the report has been finished, the DSMB Chair or NHRI will forward the formal DSMB recommendation to the Principal Investigator. It is the responsibility of the Principal Investigator to distribute the DSMB recommendation to all co-investigators and to ensure that copies are submitted to all the IRBs associated with the study.

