### 8.4. Study stopping criteria

Throughout the study period, if any SAE or serious complain happens, PI is obligated to review subject's data immediately and make medical judgment if the SAE is vaccine-related or not. If any of the following situations occurs, PI must inform the DSMB and NHRI/CRO and study recruitment should be suspended until further notice.

- (1) Any subject with severe local reaction, including ulceration, abscess or necrosis.
- (2) Any subject develops laryngospasm, bronchospasm or anaphylaxis.
- (3) Two of more subjects develop severe urticaria.
- (4) Any vaccine-related SAE during study period.

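### The DSMB rule for opening Part II in 8.3.2 tests only for SAEs, so it can contradict the stopping criteria in 8.4 and the no-safety-concern condition in 3.3

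*Protocol*

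**What the plan says.** Section 8.3.2 has the DSMB review the safety data of the 10 Part I subjects 14 days after the last second dose. It then gives the rule: "If no SAE happens prior to interim analysis, the DSMB will recommend continuation of the study recruitment for Part 2". The next paragraph requires the principal investigator to tell the DSMB of any vaccine-related SAE or serious complaint, and continues: "The DSMB is to make a decision on whether the SAE meets the stopping criteria of the study". The DSMB is also to "conclude if further enrollment of the subjects in the study should be continued or suspended".

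Section 8.4 lists four criteria. If any is met, "study recruitment should be suspended until further notice". The first is "Any subject with severe local reaction, including ulceration, abscess or necrosis". The second is laryngospasm, bronchospasm or anaphylaxis in any subject. The third is "Two of more subjects develop severe urticaria". The fourth is any vaccine-related SAE.

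Section 8.3.5 gives two forms for the DSMB report: "the study should continue without any changes, or" that it should be stopped because a protocol stopping rule has been met. Section 8.3.1 foresees recommendations on continuation, termination or other modifications, and says that the stopping rules are defined in 8.3.3. Section 3.3 and the synopsis allow Part II only in the absence of safety concerns. Section 10.7 requires DSMB review and approval of the interim report first.

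**The concern.** The interim review is the only planned safety gate between the 10 subjects of Part I and the 50 of Part II, and safety is the primary objective. The DSMB's rule at that gate should give one answer when a listed stopping criterion has been met. As written, 8.3.2 looks only at whether an SAE has occurred, while 8.4 acts on named reactions whether or not they are serious. A DSMB following 8.3.2 literally would recommend continuation while 8.4 holds recruitment suspended. What is at stake is the clarity of the DSMB's instruction, and with it the protection of Part II subjects. No analysis or estimate is affected.

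**Working it through.** The plan gives no figure to reproduce, so the check is a comparison of text.

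**Can 8.4 be met without an SAE?** Only criterion (4) uses the term. Table 7-3 grades severity, and 7.3.6 defines seriousness separately: death, threat to life, inpatient admission, disability, birth defect, or an important medical event by judgment. Among the exceptions to the hospitalization item, 7.3.6 lists "treatment on an emergency outpatient basis for an event not fulfilling any of the definitions of a SAE given above" and not leading to admission. That exception does not show that an abscess or severe urticaria is never an SAE, because the important-medical-event route stays open for criteria (1), (2) and (3). It does show that emergency outpatient care alone does not make an event serious. An injection-site abscess treated without admission and not judged an important medical event therefore meets criterion (1) and is not an SAE. Two such cases of severe urticaria meet criterion (3). Anaphylaxis would usually be judged serious.

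**What each section directs, by case:**

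| Case before the interim review | 8.3.2 rule | 8.4 | 8.3.5 | 3.3 |
|---|---|---|---|---|
| Abscess, or two severe urticarias, not SAEs | Recommend continuation | Suspend | Stop report | Part II should not open |
| Other safety concern outside 8.4, no SAE | Recommend continuation | Silent | No ground for a stop report, no outcome for a modification | Part II should not open |
| SAE judged unrelated to vaccine | Condition fails, no result stated | Not met | No ground for a stop report | Depends on judgment |
| Vaccine-related SAE | Condition fails; next paragraph applies | Suspend | Stop report | Part II should not open |

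The first row is a direct contradiction. The second shows that 8.3.2 is narrower than 3.3 even where 8.4 is not met. The third is a gap: 8.3.2 refers to any SAE, but 8.4(4) covers only vaccine-related ones.

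**Cross-reference.** Section 8.3.3, cited in 8.3.1 for the stopping rules, describes the meeting format and contains no stopping rule. The rules are in 8.4.

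**Report outcomes.** Section 8.3.5 ties its stop outcome to the protocol's stopping rules. Those are in 8.4, whose only stated consequence is suspension of recruitment, so a stop report can be read to include suspension. The modifications in 8.3.1 match neither outcome.

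**Counts.** Criteria in 8.4 not worded as SAEs: 3 of 4. Share of subjects behind the gate: 50/60 = 0.83.

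**The case against.** The strongest reply is that 8.3.2 does not stand alone. Section 8.4 suspends recruitment by itself and has the investigator inform the DSMB. Section 8.3.5 makes any stopping criterion, serious or not, a ground for a stop report. Section 3.3 and the synopsis require the absence of safety concerns. The DSMB reviews all safety data of the ten subjects, and 8.3.2 also makes serious complaints reportable, so its later mention of the SAE alone may be loose drafting. The DSMB is advisory and the sponsor decides. All of this stands, and it limits the consequence. It does not remove the contradiction: these provisions point one way, and the sentence that fixes the DSMB's recommendation can point the other.

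A reader might infer three stronger things, and the protocol supports none of them:

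- That Part II would be forced open after a stopping event. It would not, for the reasons above.
- That nothing else in 8.3 reaches non-serious stopping events. Section 8.3.5 does.
- That the DSMB report cannot express a suspension. The stop outcome can reasonably be read to include it, so only modification clearly lacks an outcome.

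The counts of 3 in 4 and 83% describe how much of the list and of the trial the rule touches. They do not measure risk.

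**Conclusion.** Wrong as written. The recommendation rule in 8.3.2 is narrower than 8.4, 8.3.5 and 3.3, and can contradict them. It leaves three of the four stopping criteria untested unless the event is also an SAE, at the step that gates 50 of 60 subjects. The wrong reference in 8.3.1 and the missing modification outcome in 8.3.5 are lesser faults in the same procedure. The conclusion rests on reading 8.3.2 literally and on one assumption: that some events under criteria (1) to (3) would not be judged important medical events under 7.3.6. The protocol gives no event rates, so no probability is claimed.

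**What to change.** - **8.3.2, recommendation rule.** Replace it with: *If no SAE has occurred, no criterion in Section 8.4 has been met and the DSMB has no other safety concern (Section 3.3), the DSMB will recommend continuation; otherwise it decides case by case, including for an SAE judged unrelated to vaccine.*
- **8.3.2, next paragraph.** Have the DSMB decide whether the *event*, not the SAE, meets the stopping criteria.
- **8.3.1.** Correct the stopping-rule reference from 8.3.3 to 8.4.
- **8.3.5.** Add an outcome *continue with stated modifications*, and state that *stopped* includes recruitment remaining suspended.
- **8.4.** Leave the four criteria unchanged, including the single-subject trigger in criterion (1).

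The cost is wording in three subsections, agreed with the DSMB before the first vaccination. If the protocol is already approved, section 17 requires IRB approval for amendments that bear on subject risk. No visits, data or subjects are added.

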### **8.3.3. DSMB meeting format**

The meetings could be performed using web/telephone conference. All slides will however be distributed to the individual members of the DSMB prior to the meeting. The DSMB meeting should be scheduled to take place 14 days after the last given injection of subject in Part I. All study data, by the latest 14 days after the last given injection, must be recorded in the CRF and be in-house at Qualitix.

Only DSMB members and the responsible biostatistician will attend this session. The meeting objective is to review data and discuss the data summaries and make recommendations.

### **8.3.4. Meeting materials**

The interim data will be reviewed in a closed session. The Closed Session Report is confidential and marked accordingly. The reports will list and summarize safety data and describe the status of the study. All meeting materials should be sent to the DSMB and the NIA at least 3 days prior to the meeting. The reports are numbered and provided in sealed envelopes within an express mailing package or by secure email as the DSMB prefers.

Copies of reports distributed prior to and during this meeting will be collected by the responsible biostatistician at the end of the Closed Session. Reports distributed to telephone and videoconference participants should be returned or as agreed to the responsible biostatistician for destruction.

### 8.3.5. Reports from the DSMB

The results from the DSMB will be distributed in a pre specified way without any possibilities for changes. The formal DSMB report should indicate that:

- ◆ the study should continue without any changes, or
- ◆ the study should be stopped\* if any of the criteria occur that are defined as study stopping rules in the protocol.

\* This recommendation should be made by formal majority vote. If this should be the case, a specified report will be created and distributed to the NHRI.

Once the report has been finished, the DSMB Chair or NHRI will forward the formal DSMB recommendation to the Principal Investigator. It is the responsibility of the Principal Investigator to distribute the DSMB recommendation to all co-investigators and to ensure that copies are submitted to all the IRBs associated with the study.

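### The formal DSMB report (8.3.5) and the no-SAE rule (8.3.2) tell the board to recommend less than its remit in 8.3.1, the stopping criteria in 8.4 and the Part II condition in 3.3 require

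*Protocol*

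**What the plan says.** Section 8.3 of the protocol gives the DSMB an advisory role, which includes to "evaluate the suitability of second part of study". Section 8.3.1 asks it to recommend continuing, terminating "or other modifications of the trial based on the observed adverse events/serious adverse events of the vaccination under study". The same list has the board "review interim analyses in accordance with stopping rules, which are clearly defined in" section 8.3.3.

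Section 8.3.2 sets the decision rule for the Part I review: "If no SAE happens prior to interim analysis, the DSMB will recommend continuation of the study recruitment for Part 2". For vaccine-related SAEs or serious complaints at any time, it has the board "conclude if further enrollment of the subjects in the study should be continued or suspended". It closes with: "The sponsor is responsible to make the final decision about further enrollment and continuation of the study".

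Section 8.3.5 lists what the formal report should state. One outcome is that "the study should continue without any changes". The other is that the study should be stopped "if any of the criteria occur that are defined as study stopping rules in the protocol". No third outcome is listed.

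The stopping criteria are in 8.4: a severe local reaction such as an abscess; laryngospasm, bronchospasm or anaphylaxis; severe urticaria in at least two subjects; and any vaccine-related SAE. The stated action is to suspend recruitment. Section 3.3 makes Part II conditional on there being no safety concerns, and 10.7 makes it conditional on DSMB review and approval of the interim report. Section 5.6 leaves to the DSMB whether the CPK visits (2a and 4a) are repeated in Part II.

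**The concern.** The board's remit, its decision rule and its report form do not match. Section 8.3.1 provides for modifications, but the report in 8.3.5 cannot express one. Sections 3.3 and 10.7 allow Part II to be held back on grounds wider than 8.4, but the report has no outcome for that. Section 8.3.2 bases the recommendation on SAEs alone, although most of the 8.4 criteria are not defined by seriousness.

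Under 8.3.5 the recommendation goes to the Principal Investigator and on to the co-investigators and the IRBs. At stake is whether, at the main safety review of a trial in healthy volunteers, that document can say what the board has concluded. A board that followed 8.3.2 and 8.3.5 literally could report unchanged continuation when other sections require recruitment to pause.

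**Working it through.** There is no figure in the plan to reproduce. The check sets the sections side by side, with simple counts for scale.

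**Scale (Table 6-1).**
- Part I, Group A05: 1 + 1 + 3 = 5. Group B10: 0 + 1 + 4 = 5. Total 10.
- Enrolled after the DSMB review: 25 + 25 = 50 of 60, and 50/60 = 83%. Of these, 25 receive 10 µg.

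**Which 8.4 criteria depend on seriousness.** Only criterion (4) is worded in terms of an SAE. Criteria (1) to (3) are not, so 3 of 4 can in principle be met without one. For criterion (2) this is weak in practice: 7.3.6 counts life-threatening and important medical events as SAEs, and anaphylaxis would often qualify. The clearer examples are a non-serious abscess under (1) and two non-serious cases of severe urticaria under (3).

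**What 8.4 leaves out.** Table 7-1 lists 9 solicited general AEs, and 8.4 names none of them. A Grade 3 systemic reaction meets 8.4 only if it is classed as an SAE under 7.3.6 and judged vaccine-related.

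**Three situations at the Part I review, none with an SAE:**

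| Situation | 8.4 / 3.3 / 10.7 | 8.3.2 | 8.3.5 |
|---|---|---|---|
| No 8.4 event, no safety concern | Part II may open once approved | recommend continuation | continue unchanged |
| Non-serious 8.4 event (abscess, or two cases of severe urticaria) | recruitment suspended | recommend continuation | stop is available; suspension is not listed |
| Safety concern outside 8.4 (e.g. Grade 3 systemic reactions mainly at 10 µg, or raised CPK) | Part II stays closed (3.3); approval can be withheld (10.7) | recommend continuation | only unchanged continuation |

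The first row is consistent. In the second, 8.3.2 conflicts with 8.4. In the third, 8.3.2 conflicts with 3.3, and 8.3.5 offers neither the modification that 8.3.1 foresees nor a way to withhold approval. The conflict with 10.7 is milder, because 10.7 sets a condition of approval and not a separate safety criterion. It still implies that approval can be refused.

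**CPK visits.** Section 5.6 gives the DSMB a decision about Part II procedures, and 8.3.5 has no outcome for reporting it. One could argue that either choice is already foreseen and so is no change, which makes this a supporting point only.

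**Cross-reference.** Section 8.3.1 places the stopping rules in 8.3.3, which covers the meeting format. They are in 8.4. This is editorial.

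**The case against.** The strongest reply is that the safeguards work regardless of the report wording. Sections 3.3 and 10.7 set necessary conditions for opening Part II. The board is advisory and the sponsor makes the final decision. Section 8.4 suspends recruitment on its own terms, and 3.3 allows suspension at any time on any safety concern. This stands. A reader might infer that the protocol gives opposite answers on whether Part II may open, but the documents do not support that: a recommendation to continue does not satisfy the separate condition in 3.3.

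A reader might also see a further conflict after an SAE judged unrelated to vaccine, because the 8.3.2 condition then fails while 8.3.5 leaves only continuation. That does not hold either. Section 8.3.2 states when the board will recommend continuation; it does not say that an SAE rules it out. If the board has no other concern, continuing is consistent with every section. If it has one, this is the gap already shown for concerns outside 8.4.

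Section 8.3.2 also provides a route for serious complaints, so escalation is not confined to SAEs. That is correct, but a complaint is not an 8.4 criterion, so the route adds no outcome to the report.

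Finally, a DSMB charter might settle the matter, or a sensible board might read the text flexibly. No charter is at hand, and the protocol itself fixes the report outcomes and the interim rule. Flexible reading would mean departing from 8.3.5 or 8.3.2 as written.

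**Conclusion.** The point holds as a fault in what the board is told to recommend. Section 8.3.5 contradicts 8.3.1 and has no outcome for withholding approval of Part II on a concern outside 8.4. Section 8.3.2 is wrong as written: with no SAE it directs continuation even when 8.4 suspends recruitment or 3.3 keeps Part II closed. It is not a failure of the Part II safeguard, which still holds.

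The consequence is a possible wrong recommendation to investigators and IRBs, based on 10 subjects and ahead of 50 of the 60 enrollments. How likely that is cannot be estimated from the protocol. The conclusion assumes that the 8.3.5 list is meant as complete, as its two alternatives suggest, and that an abscess or severe urticaria can occur without meeting 7.3.6. It should be corrected, because it concerns a safety decision in healthy volunteers and the correction is small.

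**What to change.** - **8.3.5:** keep the stop outcome, since 8.3.1 expects the board to be able to recommend termination. Replacing it with suspension would remove that. Add two outcomes, both available on any safety concern: *continue with specified modifications*, and *suspend enrollment / do not open Part II pending further review*. The first can also carry the decision on CPK visits.
- **8.3.2:** replace the no-SAE sentence with: *If there is no SAE, no criterion in 8.4 is met and there is no other safety concern, the DSMB will recommend continuation of recruitment for Part 2; otherwise it decides case by case.*
- **8.3.1:** change the reference for the stopping rules from 8.3.3 to 8.4.

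The cost is two added outcomes, one sentence, one cross-reference and the matching DSMB report form. Visits, data collection and sample size are unaffected.
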